### **11.3. Sample Size Determination**

An 88ms difference in cT1 (co-primary endpoint) is related with a 2-point change in the histological NAFLD activity score and a 1-point difference in histological ballooning (the main NASH feature). In our ongoing pre-post pilot of TDR in NASH with fibrosis stage 2-3 (LiFT), cT1 reduced by a median of 130ms (SD of change: 70ms) at 12 weeks with similar estimates among the few participants who have already completed the 24-week follow-up.

Given the more advanced stage of the disease, 22 participants (n=15 intervention, n=7 control) will allow detecting a more conservative between-group difference of 100ms (SD: 70ms) with 90% power at 5% level. Assuming approximately a 10% dropout at 24 weeks as we observed in LiFT, 24 participants are needed (n=16 intervention, n=8 control).

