### **11.2. Description of the Statistical Methods**

A table will present the baseline characteristics. This table will include age, sex, ethnic group, weight, BMI, education, marital status, smoking status, health conditions, alcohol consumption, liver markers, and summary of medication. Continuous variables will be summarised using means and standard deviations. Medians with interquartile ranges will be presented where appropriate. Categorical variables will be summarised using counts and percentages. Data will be analysed using appropriate statistical software.

All randomised participants be included in the main analysis. Missing data will be imputed using appropriate methodology. Data will be plotted in before-after plots and visually inspected for changes in continuous outcomes. The percentage of participants with evidence of worsening in each liver outcome and the extent of this worsening will be reported.

Given the sample size, it is expected that the data will not be normally distributed and the statistical power to detect differences beyond the primary outcome will be limited.

Descriptive statistics ((mean [SD], median [IQR], count [%])) on each outcome, as appropriate, will be presented stratified by baseline cT1, Child-Pugh score, MELD score, diabetes status, and median BMI.

Where appropriate, continuous endpoints will be assessed with linear mixed effects models adjusting for treatment group and baseline value and binary endpoints will be assessed with the Cochran–Mantel–Haenszel test.

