### **11.7. The Level of Statistical Significance**

The level of statistical significance will be set at  $p < 0.05$ . There will be no adjustment for multiple testing. The 95% confidence intervals will be presented but regarded nominal and descriptive.

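### Section 11.3 claims 90% power for cT1 without stating test, sidedness or baseline correlation; an unadjusted two-sided 5% t-test gives about 84%

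*Protocol*

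**What the plan says.** Section 11.3 bases the sample size on cT1, one of three co-primary endpoints. The variability comes from the ongoing pre-post pilot, in which "cT1 reduced by a median of 130ms (SD of change: 70ms) at 12 weeks". The design claim is that "22 participants (n=15 intervention, n=7 control) will allow detecting a more conservative between-group difference of 100ms (SD: 70ms) with 90% power at 5% level". Allowing for about 10% dropout, the section then sets recruitment at 24, as 16 intervention and 8 control.

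The phrase "with 90% power at 5% level" is all that is said about the error rates. Section 11.7 fixes the significance level at p < 0.05 without adjustment for multiplicity and says of precision: "The 95% confidence intervals will be presented but regarded nominal and descriptive". Section 11.2 plans linear mixed models for continuous endpoints, adjusted for treatment group and baseline value. It also remarks that "the statistical power to detect differences beyond the primary outcome will be limited".

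**The concern.** All the inputs to the power figure are printed, so it can be checked, and the usual two-sided calculation does not return 90%. A 5% level reported with 95% confidence intervals corresponds to a two-sided test; a one-sided 5% test would correspond to a 90% interval. The protocol never declares a one-sided test. One would also fit poorly with the trial's purpose, since the background (section 5) and lay summary (section 2) give possible worsening of the liver under rapid weight loss as a main reason for doing the trial.

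What is at stake is how a null cT1 result is read. cT1 is the only endpoint with a power calculation. A reader who trusts 90% will take a non-significant difference as stronger evidence against a 100 ms effect than the design provides.

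**Working it through.** **Inputs, all from section 11.3:** 15 intervention and 7 control participants evaluable; difference 100 ms; SD 70 ms (an SD of change); 5% level; stated power 90%. Sidedness and test are not given.

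**Common quantities.** Standard error = 70 × √(1/15 + 1/7) = 70 × 0.4577 = 32.04 ms. Noncentrality = 100 / 32.04 = 3.121. Degrees of freedom = 15 + 7 − 2 = 20. Power is the probability that a noncentral t variable (20 df, noncentrality 3.121) exceeds the critical value. In the normal approximation it is Φ(3.121 − z).

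**Reproducing the plan's figure (15 versus 7).**

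| Calculation | Critical value | Power |
|---|---|---|
| One-sided 5%, t | 1.725 | 91.4% |
| One-sided 5%, normal | 1.645 | 93.0% |
| Two-sided 5%, t | 2.086 | 84.3% |
| Two-sided 5%, normal | 1.960 | 87.7% |

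A simulation of 200,000 trials agrees with the t results (84.3% two-sided, 91.5% one-sided). In an unadjusted comparison, the stated 90% is met only by the one-sided test.

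**If nobody drops out.** With 16 versus 8, the noncentrality is 100 / (70 × √(1/16 + 1/8)) = 3.299 on 22 df. Two-sided power is 88.3% by t-test and 91.0% by normal approximation. So the t-test falls short even with everyone analysed. The normal approximation passes 90% there, but section 11.3 attaches its claim to 15 versus 7.

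**What 90% would require (two-sided t-test).**
- With 15 versus 7 and SD 70 ms: a difference of about 109 ms.
- With 15 versus 7 and 100 ms: an SD of about 64 ms.
- With 100 ms and SD 70 ms: 25 evaluable participants split 16 and 9 (90.7%), or 26 split 17 and 9 (91.4%).

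For the 88 ms that section 11.3 links to histological change, 15 versus 7 gives 74.3%.

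**Allowing for the planned baseline adjustment.** If baseline and change have correlation ρ, the residual SD is 70 × √(1 − ρ²) and one degree of freedom is lost (19 df). The protocol gives no ρ, so these values are assumptions:

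| Assumed ρ | Residual SD (ms) | Two-sided power, 15 versus 7 |
|---|---|---|
| 0.2 | 68.6 | 85.6% |
| 0.3 | 66.8 | 87.3% |
| 0.4 | 64.2 | 89.8% |
| 0.5 | 60.6 | 92.7% |

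The 90% mark is crossed at ρ of about 0.41.

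**The case against.** The best defence is that the protocol never says its 5% is two-sided. The confidence intervals in section 11.7 are expressly descriptive, so they suggest two-sidedness without declaring it, and a one-sided 5% test does deliver just over 90%. This stands to the extent that a reader who infers that the 90% is simply an arithmetical error goes too far. The documents support a narrower statement: the figure has no stated basis and fails on the reading that section 11.7 implies.

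It is also tempting to conclude that only a one-sided test can reach 90%, or that one was in fact used. Neither follows. Section 11.2 plans baseline adjustment, and a correlation near 0.4 would be enough. Nor can the source of the figure be identified: a two-sided normal approximation with equal allocation also gives 22 (11 + 11). However, section 11.3 uses an unadjusted SD of change and mentions no correlation, so the printed figure cannot be said to rest on adjustment.

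A further defence is that this is a feasibility trial seeking indicative evidence, and that the progression criteria in section 11.10 cover recruitment, adherence, retention and safety. That is correct, and it limits the consequence. A reader might infer that a go/no-go rule turns on the cT1 power; none does.

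Finally, the remark in section 11.2 about power beyond the primary outcome could be taken as a claim that all three co-primaries are powered. Section 11.3 confines the calculation to cT1, so this is loose wording and not a second error.

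The separate SAP may define the test, but it would not supply the basis missing from a power figure printed in the protocol.

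**Conclusion.** The point holds as a moderate one. For 15 versus 7, 100 ms and SD 70 ms, an unadjusted two-sided 5% comparison has 84.3% power by t-test (87.7% by normal approximation), not 90%. The type II error is 100 − 84.3 = 15.7% against the implied 10%, a gap of 5.7 points by t-test or 2.3 points by normal approximation. This takes the two-sided reading from the 5% level and 95% intervals in section 11.7, and assumes a common SD of 70 ms with no credit for baseline adjustment. A declared one-sided test, or a justified baseline-change correlation of about 0.4, would support 90%; the protocol gives neither. The effect is confined to the interpretation of a null cT1 result.

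**What to change.** Keep the sample size and restate section 11.3 along these lines: *22 evaluable participants (15 versus 7) give about 84% power for a 100 ms difference (SD 70 ms) with a two-sided 5% t-test; 90% power applies to a difference of about 109 ms.* If the sponsor prefers to keep 90%, section 11.3 should state what supports it: either the one-sided test, reconciled with the 95% intervals in section 11.7, or the assumed baseline correlation and its source.

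Optionally, in section 11.2, say that power is limited *beyond cT1*, since cT1 is the only co-primary with a calculation.

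The cost is a wording change in the protocol, carried into the SAP if it repeats the figure. The downside is that the stated power becomes less favourable. Recruitment, conduct and the progression criteria are unaffected.

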### **11.4. Analysis populations**

All randomised participants be included in the main analysis. A per protocol analysis will include the sub-sample of intervention participants who achieved ≥10.0% weight loss at 4 months. The adverse event analysis will include the participants commencing the intervention.

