| Exploratory objectives

To examine changes in medication                                                                                                                                                                                                                                                                                                                                                                          | Adjustment in the number and dose of medication                                                                                                                                                                                                                                                                                                                                                     | 0, 4, 16, & 24                                                                                                                                                                                                      |

|                                                |                                                                                                                                        |                                         |
|------------------------------------------------|----------------------------------------------------------------------------------------------------------------------------------------|-----------------------------------------|
| To examine changes in cardiometabolic markers  | i. Blood pressure
ii. HbA1c
iii. Lipid profile                                                                                   | 0, 4, 16, & 24
0, 16, & 24
0 & 24 |
| Process measures                        |                                                                                                                                        |                                         |
| To examine feasibility of recruitment          | i. Number of potentially eligible participants
ii. Proportion of eligible participants randomised
iii. Reasons for non-enrolment | 0
0
0                             |
| To examine intervention engagement             | i. Proportion of sessions attended
ii. Reasons for non-engagement                                                                   | 0, 4, 16, & 24                          |

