### 11.10. Progression criteria to a full trial

|   | Criterion Decision                                                                                                                | Green Progress                                                             | Amber Progress with changes | Red Stop |
|---|-----------------------------------------------------------------------------------------------------------------------------------|----------------------------------------------------------------------------|-----------------------------|----------|
| 1 | Recruitment
(Proportion of eligible patients that have been randomised)                                                        | ≥25%                                                                       | 11-24%                      | ≤10%     |
| 2 | Adherence
(Proportion of participants in the intervention group who commenced the programme with ≥10% weight loss at 16 weeks) | ≥60%                                                                       | 46-59%                      | ≤45%     |
| 3 | Retention
(Proportion of randomised participants completing a 24-week follow-up visit)                                         | ≥85%                                                                       | 66-84%                      | ≤65%     |
| 4 | Safety profile                                                                                                                    | Based on adverse and serious adverse reactions. Adjudicated by the TSDMEC. |                             |          |

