### **16.4. Other Ethical Considerations**

Observational data show that NASH resolves and early-stage fibrosis improves at one year in 90% and 45%, respectively, of patients with at least 10% weight loss at one year. The intervention under examination here has been previously shown to achieve this weight loss in almost half of the participants with rapid weight loss at the early phase. Previous studies that have given rise to the belief that rapid weight loss may worsen liver inflammation and fibrosis have provided extreme energy deficits and, in one case, providing hospitalised participants with no food at all. Our aim is to observe whether this occurs with more modest energy restriction in patients with CC-NAFLD. However, we observed no such concerns in our ongoing LiFT trial in patients with moderately severe liver disease (NASH and moderate fibrosis). We will follow-up participants with a detailed investigation at 4 weeks, 16 weeks, and 24 weeks to check for changes in their liver disease using blood tests as well as MR scans at 24 weeks.

In the unlikely event of seeing any structural abnormalities on a scan or blood test, these will be checked by a clinical specialist. If the abnormality is deemed medically important, the research team will refer the participant to their clinical care team who will discuss the implications with the participant and arrange for further investigations as necessary. Participants will not be informed unless the doctor considers the finding has clear implications for their current or future health. It is important to note that scans are not carried out for diagnostic purposes, and therefore the scans are not a substitute for a clinical appointment. Rather, the scans are intended for research purposes only.

AEs during the intervention period have previously shown to be infrequent and disappear over time (see section 10). The dietitian will support the participants based on current clinical guidance during the consultations in managing potential AEs. The research team will handle the AEs when reported in a sensitive manner and will communicate these to the hepatology clinical team in line with section 9.7, 9.9, 10, and 13.3.2.

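### The per-protocol set is a weight-loss responder subgroup of one arm, and the adherence progression criterion leaves out participants who never start

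*Protocol*

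**What the plan says.** Protocol section 11.4 opens with "All randomised participants be included in the main analysis", and section 9.10 adds that withdrawal after randomisation does not remove a participant's data. Section 11.4 then defines a second set: "A per protocol analysis will include the sub-sample of intervention participants who achieved ≥10.0% weight loss at 4 months". It gives no rule for controls, no comparator and no test. Body weight is a secondary outcome in section 6, measured at weeks 0, 4, 16 and 24.

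In section 11.10, the adherence criterion for progression to a full trial is "Proportion of participants in the intervention group who commenced the programme with ≥10% weight loss at 16 weeks". It is green at 60% or more, amber at 46 to 59%, and red at 45% or less. The retention criterion in the next row of the same table is "Proportion of randomised participants completing a 24-week follow-up visit".

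Section 6 also lists "Proportion of sessions attended" as a process measure of engagement. It defines neither the per-protocol set nor the adherence criterion. Sections 2 and 5 put the feasibility question as whether patients stick to the programme.

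**The concern.** A per-protocol set is normally defined by how the protocol was followed. Here it is defined by how much weight was lost. A participant who follows the diet fully and loses 9% is outside the set. The protocol's own background treats weight loss as the route to liver benefit, so choosing intervention participants by weight loss is likely to choose those with the better liver outcome. Participants whose intervention is stopped under Appendix E would plausibly be less likely to reach 10% and would tend to fall out, in a trial whose first co-primary objective is safety signals. A later reader could take the result for a per-protocol treatment effect.

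The second issue is separate and feeds a formal decision. Someone allocated to the programme who never starts has not stuck to it, yet leaves the adherence denominator. The percentage can then only rise or stay the same. With 16 participants in the arm, single individuals decide the band.

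**Working it through.** **Inputs from the protocol.** Section 11.3: 16 intervention and 8 control participants randomised, 15 and 7 evaluable, and a "between-group difference of 100ms (SD: 70ms) with 90% power at 5% level". Section 11.10: the bands above. Section 16.4: "The intervention under examination here has been previously shown to achieve this weight loss in almost half of the participants", where the weight loss meant is at least 10% at one year, so about 8 of 16.

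**Assumed, because the protocol gives no figure.** The correlation r between weight loss and cT1 fall within the intervention arm (0.3 to 0.7), and the number of non-starters (0 to 5 of 16).

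**1. The plan's own figure.** With 2:1 allocation, two-sided 5% and 90% power, the normal formula gives a control group of 1.5 × (1.960 + 1.282)² × (70/100)² = 7.7, so 8 + 16 = 24 (23.2 before rounding). The stated evaluable number is 22. Power at 15 and 7 is 87.7% (two-sided, normal), 84.3% (two-sided, t) or 91.4% (one-sided, t). The figure is reproduced closely enough to use 100 ms and 70 ms as yardsticks. Nothing below depends on it further.

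**2. Selection in the per-protocol set.** If weight loss and cT1 fall are bivariate normal and the top share s by weight loss is kept, the kept group's mean cT1 fall exceeds its own arm's mean by

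r × SD × φ(c) / s, where c is the cut-off that leaves share s above it.

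For s = 0.5, c = 0 and φ(0)/0.5 = 0.798, so the excess is r × 70 × 0.798 = r × 55.9 ms. For s = 0.6 the multiplier is 0.644, so the excess is r × 45.1 ms.

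| r | Excess, half kept | Excess, 60% kept | Favourable p<0.05, half kept |
|---|---|---|---|
| 0 | 0 ms | 0 ms | 2.4% |
| 0.3 | 16.8 ms | 13.5 ms | 6.6% |
| 0.5 | 27.9 ms | 22.5 ms | 12.1% |
| 0.7 | 39.1 ms | 31.6 ms | 20.1% |

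The last column is from 20,000 simulated trials per row with no treatment effect on cT1. The kept participants out of 16 were compared with all 8 controls by a two-sided t-test. In the comparison of all randomised participants the expected bias is 0.

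**3. The adherence denominator.** With all 16 as denominator, green needs at least 10 successes (62.5%) and red is 7 or fewer (43.8%). Removing non-starters gives:

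| Non-starters | Successes | Of all 16 | Of starters |
|---|---|---|---|
| 0 | any | unchanged | unchanged |
| 1 | 9 | 56.3%, amber | 9/15 = 60.0%, green |
| 1 | 7 | 43.8%, red | 7/15 = 46.7%, amber |
| 3 | 8 | 50.0%, amber | 8/13 = 61.5%, green |
| 5 | 7 | 43.8%, red | 7/11 = 63.6%, green |

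Suppose the true success rate among all allocated is 50%, close to the rate in section 16.4. By binomial sums, the chance of green is 22.7% with denominator 16. With the starters-only denominator it is 34.7% if each participant has a 6.25% chance of not starting, and 45.3% if that chance is 12.5%.

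**The case against.** **The main result is not affected.** This stands. A reader might infer that the trial's cT1 conclusion is biased. It is not, because the main analysis is of all randomised participants, no decision rule uses the per-protocol set, and section 11.7 calls the confidence intervals nominal and descriptive.

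**The comparison with controls is assumed.** This also stands. Section 11.4 is silent on controls, so it should not be read as dropping them or as promising a test. If the set is only described within the arm, what remains wrong is the label.

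**The size and direction are not established.** Largely right. The correlation is assumed. With truly no effect of allocation, it would all have to come from confounding, so 0.7 is hard to defend. The formula itself does not need a zero effect: under the same model it gives the excess over the arm's own mean, whatever that mean is. The favourable direction follows the protocol's premise, but section 5 also reports new fibrosis in fast weight losers on a more restrictive diet, so it cannot be taken as certain for every outcome.

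**Adherence among starters is a legitimate quantity.** True, and section 11.10 states openly which one it uses. Weight loss is also an objective proxy for following total diet replacement, and attending sessions does not prove product use. But the criterion is meant to show whether patients stick to the programme, and uptake after allocation has no criterion of its own. Retention would catch a non-starter only if that person also left follow-up.

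**A green verdict with only a minority succeeding is remote.** A reader might infer this risk from the denominator. It needs at least 5 non-starters of 16 (7/12 = 58.3% is still amber; 7/11 is green), and nothing in the protocol suggests so many. Nor is session attendance ignored, since it is a listed process measure.

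**Conclusion.** The point holds in a limited form, as two separate matters of wording.

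First, the set in section 11.4 is a responder subgroup of one arm and should not carry the per-protocol name. Compared with all controls, it would show about 17 to 39 ms of benefit from selection alone, with no true effect. That rests on half the arm being selected, an SD of 70 ms, and an assumed positive correlation of 0.3 to 0.7. It concerns a supporting analysis only.

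Second, the adherence criterion in section 11.10 can move up a band because of one non-starter among 16. This assumes only that a non-starter would not count as a success. It affects one of four progression criteria, and has no effect if everyone starts. Of the two, this matters more, because it bears on the decision to go to a full trial.

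**What to change.** In section 11.4, rename the ≥10% set a weight-loss responder subgroup and report it descriptively within the intervention arm, with no test against control. If a per-protocol analysis is kept:

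- define it by conduct already recorded, for example a stated share of sessions attended;
- label it supportive;
- state that it still conditions on events after randomisation;
- do not remove participants whose intervention was stopped on liver criteria, since that would again favour the intervention.

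In section 11.10, base the adherence criterion on all participants allocated to the intervention, count a missing week-16 weight as not achieved, and show the starters-only figure beside it.

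The cost is wording only: no new data, visits or participants. The adherence percentage will be equal or lower, so the change should be settled before any analysis.

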- Significant non-adherence with treatment regimen or trial requirements
- An adverse event which requires discontinuation of the trial intervention or results in inability to continue to comply with trial procedures
- Disease progression which requires discontinuation of the trial intervention or results in inability to continue to comply with trial procedures
- Criteria of the algorithm in Appendix E are met.
- If enhanced observation is necessary as per section 10 but is not possible

The follow-up of participants that have withdrawn from the intervention but not from active follow-up will continue with the standard follow-up assessments of the study.

If the intervention is discontinued due to criteria in Appendix E, the intervention may be re-introduced with approval of the Trial Steering, Data Monitoring, and Ethics Committee (TSDMEC) if another cause of the elevation is identified. If on re-introduction, the elevations in liver function tests persist, the intervention must be discontinued and enhanced observation must continue as per section 10. Data from randomised participants will be analysed and post-randomisation withdrawal from the study will not result in exclusion of the data for that participant from the analysis. If the participant is withdrawn before randomisation, they will be replaced (as per section 9.3). The type of withdrawal and reason for withdrawal will be recorded in the CRF. If the participant is withdrawn due to an AE, the Investigator will arrange for frequent telephone calls as agreed with the participant (or an ad-hoc study visit upon the study clinician's judgement) until the AE has resolved or stabilised (also see sections 9.7, 10, and 13.3.2). If a participant is withdrawn from treatment due to pregnancy the pregnancy will be followed-up to outcome. See the Safety Reporting section below.

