## **10. SAFETY REPORTING**

Potential AEs will be recorded at each follow-up assessment. Participants may contact the research team (e.g., over the phone) at any time point during the course of the study to report potential AEs. AEs will be recorded as part of the CRF of the subsequent study visit (e.g., an AE occurring between weeks 4 and 16 will be recorded as part of the 16-week assessment).

One previous trial reported no SAEs due to the TDR, whereas another reported two SAEs potentially related to the TDR in the same participant. There was evidence that for every five people one would experience an adverse, mostly mild, event because of the TDR programme. Constipation, headache, fatigue, and dizziness are the most common AEs albeit occurring in a minority of participants (<8% each) and disappeared over time. Less common side effects include dry mouth, abdominal pain, bad breath, diarrhoea, hair loss, dry skin, mood changes, and feeling cold.

The safety reporting window begins from the first day of the intervention for participants in the intervention group and from the day of randomisation for participants in the control group. It finishes for both groups when the participant completes the study. The limit of investigator follow-up of SAEs will be until the participant completes the study. This requirement will be the same for all SAEs.

Laboratory abnormalities without clinical significance are not recorded as AEs or SAEs. However, laboratory abnormalities that require enhanced observation, medical or surgical intervention, or lead to discontinuation of the intervention must be recorded as an AE, as well as an SAE, if applicable.

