### **11.6. Stopping rules**

The TSDMEC will formally recommend early termination if needed based on review of the AEs and SAEs. To facilitate TSDMEC decision making, the following recommendation for a pre-defined cut-off will apply. If no SAEs have occurred in the control group and the lower bound of the 95% confidence interval for SAEs is at least 30% in the intervention group based on a one-sample test for binomial proportion (Wilson score), the trial will stop.

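### The adverse-event analysis set as worded omits the control arm, and the safety window opens at different points in the two arms

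*Protocol*

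**What the plan says.** Section 11.4 sets two populations side by side. For the main analysis: "All randomised participants be included in the main analysis". For safety: "The adverse event analysis will include the participants commencing the intervention". The second sentence does not mention the control arm.

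Section 10 fixes when events begin to count. In one arm, "The safety reporting window begins from the first day of the intervention for participants in the intervention group"; in the other, "from the day of randomisation for participants in the control group". The end is shared: "It finishes for both groups when the participant completes the study".

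Other sections rely on control-arm events:

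- Section 6 lists adverse events as a secondary outcome of the randomised trial.
- Section 10.1 handles hepatic decompensation, transplantation or qualification for it, and hepatocellular carcinoma as SAEs, and gives as the reason the trial's aim concerning progression.
- Section 11.6 makes its stopping recommendation conditional on the control arm: "If no SAEs have occurred in the control group".
- Section 13.3.2 lets the oversight committee (TSDMEC) ask for AE rates by trial group.

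**The concern.** Controls receive usual care and never start the programme. An AE set defined by starting the programme therefore either contains no controls or needs an unwritten addition to bring them in. With that addition, one arm is still filtered on something that happens after randomisation and the other is not.

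The window works in the same direction. An event that occurs after randomisation but before the first diet day is reportable in a control and not in an intervention participant. A never-starter has no reporting window at all. Because the window governs what is recorded, a later analysis may be unable to recover those events.

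At stake is how AEs and SAEs are read against the background of cirrhosis. Decompensation can occur without the diet, so a list of events in starters alone cannot show an excess over background or its absence. With 24 participants, one person or one event is a visible share of an arm.

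**Working it through.** The protocol gives no figure for this point to reproduce. The check compares the sections and then sizes two consequences.

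**Inputs.** 16 intervention and 8 control participants (section 11.3). AE set (section 11.4). Window start and end (section 10). Stopping rule: no control SAEs and a Wilson 95% lower bound of at least 30% in the intervention group (section 11.6). Follow-up of 24 weeks = 24 × 7 = 168 days.

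**1. Who is in the AE set.**

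- Literal reading: at most 16 intervention participants and 0 of 8 controls, so there is no between-arm comparison.
- Charitable reading: all 8 controls plus 16 − k intervention participants, where k is the number who never start. The protocol gives no k, but it foresees non-starters: the adherence criterion in section 11.10 is restricted to those who began the programme.

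**2. What the window costs.** Let g be the days from randomisation to first diet day. If both arms finish 168 days after randomisation, the intervention arm loses g/168 of its window. With equal constant event rates, its expected event count per person relative to control is (168 − g)/168.

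| g (assumed) | Share lost | Expected ratio to control |
|---|---|---|
| 3 days | 3/168 = 1.8% | 0.98 |
| 7 days | 7/168 = 4.2% | 0.96 |
| 14 days | 14/168 = 8.3% | 0.92 |

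The direction makes the intervention look safer. The protocol does not state g. The nominal schedule points to a short gap: section 9.4 puts randomisation within 24 hours of the end of the baseline visit, section 9.6.1 starts phase 1 at week 0, and Appendix B places randomisation at week 0. The gap is not fixed at zero, because allocation is given by phone, products may be posted, and Appendix C has an initial consultation in week 0 with the diet stage listed from week 1.

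**3. How sensitive the stopping rule is to who is counted.** Section 11.6 does not say which intervention participants form its denominator, so this is an illustration only. The Wilson lower bound is

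L = [p + z²/(2n) − z√(p(1−p)/n + z²/(4n²))] / (1 + z²/n), with p = x/n and z = 1.96 (two-sided 95%).

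- 8/16: (0.500 + 0.120 − 0.273)/1.240 = 28.0%, below 30%.
- 9/16: (0.5625 + 0.120 − 0.271)/1.240 = 33.2%, above 30%.
- 8/15: (0.533 + 0.128 − 0.283)/1.256 = 30.1%, above 30%.

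Leaving out one event-free non-starter turns 8/16 into 8/15 and meets the threshold. Failing to record one pre-start SAE turns 9/16 into 8/16 and misses it. The two asymmetries can therefore move the rule in opposite directions.

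**4. Which outcomes are affected.** Section 6 defines the first co-primary outcome as severe changes in ALT, AST and total bilirubin. Nothing in section 11.4 takes that outcome out of the all-randomised main analysis. The defect is confined to AEs and SAEs.

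**The case against.** The strongest reply is that the protocol as a whole plainly intends to collect control events. Section 10 defines a window for controls, section 11.6 counts their SAEs, section 13.3.2 foresees comparison by group, and Appendix B schedules AE assessment without restricting it by arm. On that view section 11.4 is loosely worded and means a conventional safety set of starters plus controls. This largely stands as a statement of intent, and it makes the charitable reading the more likely one. It does not repair the sentence, the loss of never-starters or the unequal window.

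Three further points stand:

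- The trial is a small feasibility study with intervals labelled descriptive (section 11.7). The safety criterion for progression is adjudicated by the committee on adverse reactions (section 11.10), not by a between-arm test. Events before the first diet day cannot be reactions to the diet.
- If visit weeks in the intervention arm run from first diet day, both windows last about 24 weeks and no time at risk is lost. Only the start date differs. The protocol does not say which clock applies.
- Section 9.10 says that "post-randomisation withdrawal from the study will not result in exclusion of the data for that participant from the analysis". That concerns withdrawal, and never starting is not clearly withdrawal, so it is at most a supporting sign of intent.

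A reader might infer that the co-primary safety comparison is lost. The documents do not support this, because that outcome is biochemistry analysed in all randomised participants. A reader might also assume a gap of several weeks and hence a large bias. No section gives such a gap. If visits run from randomisation, it would put the 2-week safety visit before the diet had begun.

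The statistical analysis plan is not shown and might add a control table. Section 11.4 nevertheless fixes the set and section 10 fixes what is recorded, so the point is not simply left to that plan.

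**Conclusion.** The point holds for the secondary AE and SAE comparison and should be fixed. As written, the analysis set either excludes all 8 controls or selects the intervention arm on a post-randomisation event, and the window captures pre-start events in controls only. Both fit poorly with the SAE-based capture of decompensation, the control-dependent stopping rule and the by-group committee review.

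The set problem rests on no assumed figure. The window bias does: about 2% for 3 days and 4% for 7 days of a 24-week window, given a common end and constant equal rates. It is probably small if participants start within days. The stopping-rule examples show sensitivity only, since section 11.6 does not tie its denominator to the section 11.4 set.

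**What to change.** - **Section 11.4:** analyse AEs and SAEs in all randomised participants by allocated arm. Add a supplementary table of intervention participants from first diet day.
- **Section 10:** open the recording window at randomisation in both arms.
- **Section 11.6:** state that the intervention-group denominator is all participants randomised to the intervention.

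The cost is a few sentences and the recording of events in the short interval before the diet starts. A few pre-treatment events will appear in the intervention column, and the supplementary table separates them. The fuller denominator slightly raises the event count needed in section 11.6 (9 of 16 rather than 8 of 15 in the example), while the earlier window may add events, so the committee should see both effects before agreeing. The section 10 change should come first, because events that were never recorded may not be recoverable at analysis.
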